### Concealment mechanism {16b}

Allocation concealment will be ensured via a central web-based system (Ennov Clinical® 7.5.720). The treatment to which a patient will be allocated will be disclosed only after enrollment in the study.

### Implementation {16c}

The randomization key will only be known to the biostatistician and the data managers. Investigators at each study site will be responsible for patient enrollment in the study. Assignment of participants to each study group will be ensured by the central web-based system (Ennov Clinical® 7.5.720®) operated by local investigators, after verification of patient eligibility and inclusion in the study.

## Assignment of interventions: blinding

### Who will be blinded {17a}

Blinding of care providers will be unpracticable as knowledge of the ventilatory settings and ventilatory measurements are required to adapt care and to monitor the safety of mechanical ventilation. Outcome assessors will not be blinded as group allocation could be deducted from ventilatory settings provided in the digital medical charts. Data analysts will be blinded from group allocation, although this may be deducted from the VT measurements provided as a variable in the dataset.

### Procedure for unblinding if needed {17b}

Not applicable

## Data collection and management

### Plans for assessment and collection of outcomes {18a}

Investigators are responsible for the assessment and collection of outcomes, baseline, and other trial data. Data will be entered in the electronic case report form by delegated team members and will be monitored by trained clinical research associates. The digital version of the case report form is provided in Additional file 6. Subjects will be assessed daily while hospitalized in the intensive care unit (ICU). Day 60 assessment will be performed by investigators or delegated team members using electronic medical records and phone calls to the patient’s general practitioner and to any MD involved in patient care after ICU discharge if required. Day 365 assessment will be performed by a phone call by investigators or delegated team members, to administer 3 tests whose validity have been proven when administered remotely [15, 18, 19]. French language versions of T-MOCA [15], IES-R [17], and SF-36 [16] questionnaires will be implemented in the electronic case report form and are provided in Additional files 7, 8, and 9.

### Plans to promote participant retention and complete follow-up {18b}

Missing values for secondary outcomes assessed during ICU stay are not expected, since patients will remain hospitalized. Missing values of VFD at day 60 are not expected as this parameter will be assessed at ICU discharge. Missing values for survival day 90 or day 365 could occur for patients surviving at hospital discharge, and the subsequent procedure will be applied to minimize the number of patients with incomplete follow-up. Upon enrollment, patients’ and their next of kin’s contact information will be stored in the digital health record at each study site. Patients will be contacted by a phone call at day 90 and day 365 to assess the vital status, to perform the T-MoCA test [15], and to compute the SF-36 score and the IES-R score. In case contact with the patient is lost, study technicians will contact the patient’s next of kin or the patient’s general practitioner in order to re-establish contact or assess the vital status. Any attempt to contact the patient will be documented in the patient’s medical records.

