### Outcomes {12}

#### Primary outcome

The primary outcome is a composite score based on 90-day all-cause mortality as the first criterion and the number of VFD at day 60 after inclusion as the second criterion. The composite score will be obtained by comparing each patient of one group to all patients of the other group. For each pair, a value of + 1 (favorable), − 1 (unfavorable), or 0 (neutral) will be given to each patient. The score will be built as follows:
A value of + 1 will be given for a patient alive at day 90 paired with a patient deceased at day 90.A value of + 1 will be given for a patient alive at day 90 paired with a patient alive at day 90 but with a lower number of VFD.A value of 0 will be given for pairs with both patients deceased at day 90.A value of 0 will be given in case of an identical number of VFD for the pairs of patients alive at day 90.A value of − 1 will be given for a deceased patient in comparison with patients alive at day 90.A value of − 1 will be given for a patient alive at day 90 paired with a patient alive at day 90 but with a higher number of VFD.

For a given patient, the score will correspond to the sum of values resulting in the comparison to all patients of the other group.

VFD will be computed as follows from the day of inclusion:
VFD = 0 if the patient dies between inclusion and day 60VFD = 60 − *x* if the patient is successfully weaned from invasive mechanical ventilation, with *x* being the number of days from inclusion to last successful extubation. Successful weaning from mechanical ventilation will be defined as extubation without reintubation within at least 48 h (or weaning from mechanical ventilation for at least 48 h for patients with tracheostomy)VFD = 0 if the patient is mechanically ventilated for more than 60 days after inclusion

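### The retention section says day-60 VFD is assessed at ICU discharge and so not expected to be missing, contradicting the VFD definition and the planned day-60 assessment

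*Protocol article*

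**What the plan says.** Three places in the protocol article bear on how VFD is obtained.

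- **Retention and follow-up {18b}:** "Missing values of VFD at day 60 are not expected as this parameter will be assessed at ICU discharge". The section then accepts that survival status may be missing for patients who leave hospital alive, and provides a later contact: "Patients will be contacted by a phone call at day 90 and day 365 to assess the vital status".
- **Collection of outcomes {18a}:** "Day 60 assessment will be performed by investigators or delegated team members using electronic medical records and phone calls to the patient’s general practitioner". Where needed, physicians who take over the patient's care once the ICU stay has ended are called as well. Among the primary and secondary outcomes, VFD is the only one dated day 60.
- **Primary outcome:** the composite uses 90-day mortality first and "the number of VFD at day 60 after inclusion as the second criterion". VFD is 0 for a death up to day 60 or for ventilation beyond 60 days. Otherwise it is 60 − x, with x "being the number of days from inclusion to last successful extubation".

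The section on non-adherence and missing data {20c} plans to describe missing data and not to impute them.

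**The concern.** One component of the primary endpoint has two stated points of ascertainment, and the earlier one cannot deliver the definition. When a patient leaves the ICU before day 60, two inputs to VFD are still open: whether the patient will die by day 60, and whether the extubation already recorded will prove to be the last successful one. A patient who leaves the ICU still ventilated before day 60 has no determinable VFD at that point.

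The statement that missing values are not expected rests on this premise and fails with it. Vital status to day 60 is an input to VFD, and the same section concedes that survival status can be lost after hospital discharge. If the discharge value were kept for a patient lost afterwards, an unknown VFD would appear as a known one and would not enter the planned count of missing data.

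At stake are the pairs of the primary outcome that VFD decides, and the separate secondary VFD outcome.

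**Working it through.** **1. What each event after ICU discharge does to a VFD fixed at ICU discharge**

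| Event after ICU discharge | VFD under the definition | Value fixed at discharge | Outcome affected |
|---|---|---|---|
| Reventilated, alive at day 90 | 60 − days to the later extubation, or 0 if ventilated past day 60 | too high | primary and secondary |
| Left ICU still ventilated before day 60, alive at day 90 | depends on later weaning | not determinable | primary and secondary |
| Died by day 60 | 0 | too high if already extubated | secondary only, if day-90 vital status is known |

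The last row follows from the scoring rule: "A value of − 1 will be given for a deceased patient in comparison with patients alive at day 90". Two deaths score 0. VFD is not consulted for a patient known to have died by day 90.

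**2. Share of pairs decided by VFD**

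Inputs from Sample size {14}: 90-day mortality 45% (control) and 40% (intervention).

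- Both alive, decided by VFD: 0.55 × 0.60 = 0.33
- Exactly one dead, decided by mortality: 0.45 × 0.60 + 0.55 × 0.40 = 0.49
- Both dead, tied: 0.45 × 0.40 = 0.18

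VFD decides about 33% of all pairs, or 0.33 / 0.82 = 40% of pairs not tied by double death.

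**3. Planned net benefit**

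The protocol states no net benefit (wins minus losses, as a share of pairs), so it is derived here. Assumption: VFD in survivors is normal with the {14} values, 28 (SD 16.5) and 34.5 (SD 13).

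- Mortality part: 0.60 × 0.45 − 0.40 × 0.55 = 0.05
- VFD part: z = 6.5 / √(16.5² + 13²) = 6.5 / 21.0 = 0.309 and Φ(z) = 0.6215, so 0.33 × (2 × 0.6215 − 1) = 0.080
- Total: 0.05 + 0.08 = 0.13 (win probability, ties counted as half: 0.5 + 0.13 / 2 = 0.565)

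Truncating VFD to 0–60 gives 0.125 instead.

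**4. Shift from one misrecorded survivor, 100 per arm**

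For one intervention survivor recorded at r when the true value is t, the change in net benefit is 2 × 0.55 × [F(r) − F(t)] / 100. F is the control VFD distribution and 0.55 is the share of control patients alive.

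- r = 50, t = 0: 2 × 0.55 × (0.909 − 0.045) / 100 = 0.0095 (0.0097 with VFD rounded and clipped to 0–60)
- r = 50, t = 20: 2 × 0.55 × (0.909 − 0.314) / 100 = 0.0065
- r = 40, t = 30: 2 × 0.55 × (0.766 − 0.548) / 100 = 0.0024

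A control survivor recorded at 50 instead of 0 gives 2 × 0.60 × (0.883 − 0.004) / 100 = 0.0106, in the other direction. About 0.01 per patient is therefore close to the ceiling.

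**5. Errors in both arms**

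This is a simulation on the same planning inputs. Assumption, not from the protocol: a fraction of survivors has an unrecorded later reintubation costing 5–25 days.

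- 5% in each arm: win probability about 0.566 as recorded and 0.565 true
- 5% control, 15% intervention: about 0.565 as recorded and 0.555 true

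Since net benefit is twice the win probability minus 1, the differences are about 0.002 and 0.02.

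**The case against.** The strongest reply is that the plan already contains the remedy. Section {18a} is where outcome collection is specified. Its day-60 assessment uses records and calls to physicians outside the ICU, and it evidently exists to complete VFD. The sentence in {18b} only explains why few missing values are expected; it changes neither the definition nor the day-60 assessment. The case report form and the full protocol, both cited as additional files and not available here, may show that sites record what the definition needs. This largely stands: harm requires a site to act on the {18b} sentence and treat the day-60 follow-up as unnecessary. It does not remove the contradiction. The calls to post-ICU physicians are made only if required, and a reader of {18b} could conclude that they are not. The stated purposes of the day-90 call are vital status and questionnaires, with no mention of ventilation history.

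Three stronger readings are tempting, and the document does not support them.

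- **That half of the primary endpoint is at risk.** VFD is the second of two ranked criteria and decides about one third of pairs.
- **That ward deaths before day 60 distort the primary ranking.** They are ranked on mortality before VFD is used, provided the day-90 contact or its fallback to next of kin or general practitioner succeeds.
- **That the primary estimate is materially biased.** A 50-versus-0 error needs early extubation, ICU discharge, reintubation, ventilation past day 60 and survival to day 90. Accumulating such errors also needs them to fall mainly in one arm. The protocol gives no rate of these events and no reason for an imbalance.

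**Conclusion.** The point holds as a contradiction about how a component of the primary endpoint is ascertained, together with a missing-data claim that does not follow from the protocol's own definition. The consequence is conditional on sites following {18b} instead of {18a}.

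The expected effect on the primary result is small: at most about 0.01 in net benefit per misrecorded patient against roughly 0.13 planned, about 0.002 to 0.007 for the partial errors shown, and close to nothing if errors are equal in both arms. A shift of about 0.02 needed an assumed threefold imbalance. These figures rest on the planning mortality, on normal VFD in survivors and on 100 patients per arm. How often patients are reventilated or die after ICU discharge is not given and was not estimated.

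The secondary VFD outcome is more exposed, because a death between ICU discharge and day 60 would also leave a positive value where the rule gives 0, unless it is corrected from later follow-up. The point is worth correcting because the correction is nearly free, not because the trial's conclusion is likely to turn on it.

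**What to change.** Replace the VFD sentence in {18b} with a statement to this effect: VFD is derived for every patient at the day-60 assessment described in {18a}, from vital status and all episodes of invasive ventilation from inclusion to day 60, including those after ICU discharge and after readmission. Drop the claim that missing values are not expected. State that VFD is counted as missing when day-60 status is unknown, so that such patients appear in the planned description of missing data.

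The cost is a short text change and a check that the case report form captures ventilation episodes after ICU discharge. The day-60 contact is already planned, and neither the sample size nor the endpoint definition changes.

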### Data management {19}

An electronic case report form (eCRF) will be drawn up for each included patient using Ennov Clinical® 7.5.720 central web-based system. Subjects will be identified by the first letter of their first name, the first letter of their family name, the center number, and the inclusion number. This code will be the only information featured on the eCRF enabling a retrospective link to the patient. The data collected during the study will be processed electronically in accordance with the requirements of the French Data Protection Authority (CNIL) in compliance with French Reference Methodology MR001. eCRF will be transmitted electronically and centralized in the data management department of the coordinating site.

### Confidentiality {27}

Subject confidentiality is strictly held by the participating investigators, their staff, the sponsor, and their agents. This confidentiality is extended to cover clinical information relating to subjects, test results of biological samples or medical imaging, and all other information generated during participation in the study. All electronic transmission of data that leaves each study center will be identified only by a coded number that is linked to a subject through a code key maintained at the clinical site, and eventually destroyed at the end of the study. All source records including electronic data will be stored in secured systems.

No identifiable information concerning subjects in the study will be released to any unauthorized third party. Subject confidentiality will be maintained when the study results are published or presented in conferences. The study monitor, other authorized representatives of the sponsor, and representatives of regulatory agencies may inspect all documents and records required to be maintained by the investigator, including but not limited to medical records (office, clinic, or hospital) for the subjects in this study.

### Plans for collection, laboratory evaluation, and storage of biological specimens for genetic or molecular analysis in this trial/future use {33}

No biological specimens will be collected for the sake of the trial. All biological assays reported in the case report forms are those performed in the usual care of COVID-19 patients with ARDS. No biological samples will be stored for future analysis.

## Statistical methods

### Statistical methods for primary and secondary outcomes {20a}

#### Descriptive analysis

Patients’ characteristics will be described and compared between the two groups to verify the allocation efficacy. Quantitative characteristics will be described using the following statistics: number of missing data, mean, standard deviation, quartiles, and minimum and maximum values. Qualitative characteristics will be described using the following statistics: number of missing data and absolute and relative frequency in each category. Quantitative characteristics will be compared between the two groups using the *t* test of Student or the test of Mann and Whitney. Qualitative characteristics will be compared using the *χ*^2^ test or the exact test of Fisher.

#### Analysis of the primary outcome

The main analysis will be carried out by intention to treat, i.e., all the patients included in the study will be analyzed in their initial randomization group regardless of whether the allocated ventilation strategy was effectively applied or not.

The distribution of the composite score will be described in each group using the following statistics: mean, standard deviation, quartiles, and minimum and maximum values. It will be compared between the two groups using the test of Mann and Whitney.

The ULTV effect size will be quantified by the probability of a favorable result for a patient belonging to the ULTV arm in comparison with a patient belonging to the protective ventilation arm. This probability will be estimated by the proportion of pairs for which the patient of the ULTV arm will have a favorable result [20]. This estimate will be given with a 95% confidence interval.

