### Sample size {14}

The sample size was computed through data simulations based on the following hypotheses:
Ninety-day mortality 45% in the control group, and 40% in the intervention group (i.e., relative reduction 11%)Mean ± standard deviation (*SD*) VFD at day 60 28 ± 16.5 in the control group and 34.5 ± 13 in the intervention group

The expected mortality in patients with COVID-19 and moderate to severe ARDS is between 34 and 50% [1]. The mean and *SD* of VFD at day 60 in the control group was taken from the subgroup of patients with PaO_2_/FiO_2_ < 150 mmHg included in the control group of the prospective randomized Xtravent-study comparing ultra-protective ventilation with extracorporeal CO_2_ removal versus conventional protective ventilation [7]. To be conservative, we have chosen to take an expected difference between the two groups of the present study corresponding to 50% of the difference observed in the Xtravent-study between the control and the intervention groups.

For each scenario corresponding to a given sample size, 1000 datasets were simulated. For each simulation, the score was computed for each patient and compared between the two groups using the test of Mann and Whitney. The power was computed as the proportion of tests with a bilateral *p*-value < 0.05.

The results of the simulations allowed us to determine that the inclusion of 100 patients per group will achieve a power greater than 80% to conclude a significant difference between the groups.

The simulations were implemented by two biostatisticians with the SAS software, version 9.4 (Copyright (c) 2002–2003 by SAS Institute Inc., Cary, NC, USA) and the R software, version 3.6.1 (R Core Team (2012)). The results were similar.

To account for premature exits from the study (withdrawal of informed consent for example), we have planned to add 10% more patients (10 supplementary patients in each group for a total of 220 patients).

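### The primary effect size counts tied pairs as non-wins, so its no-effect value is not fixed: about 0.40 at the planned 45% mortality, and moving with mortality

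*Protocol article*

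**What the plan says.** Under Outcomes {12}, Primary outcome, the protocol article builds the score from pairwise comparisons: "For each pair, a value of + 1 (favorable), − 1 (unfavorable), or 0 (neutral) will be given to each patient". Two kinds of pair are neutral. The first: "A value of 0 will be given for pairs with both patients deceased at day 90". The second: "A value of 0 will be given in case of an identical number of VFD for the pairs of patients alive at day 90". A patient's score is the sum of these values over all patients of the other arm.

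Under Analysis of the primary outcome, the score is described in each arm (mean, SD, quartiles, range) and compared by a Mann-Whitney test. The effect size is the probability of a favorable result for a ULTV patient compared with a control patient, and its estimator is given: "This probability will be estimated by the proportion of pairs for which the patient of the ULTV arm will have a favorable result". A 95% confidence interval is promised. The section gives no weight for neutral pairs and no no-effect value, and it does not ask for loss and tie shares.

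**The concern.** Favorable is a defined term in this protocol: it means +1. Taken as written, the estimator divides the number of ULTV wins by the number of all pairs, so a tie counts the same as a loss.

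Ties are built into this design. With 40–45% of patients expected to die by day 90, close to a fifth of all pairs are neutral because both patients are dead. Equal VFD adds a little more, including pairs of survivors who both have VFD of zero.

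A probability of doing better than a patient in the other arm is usually read against one half. This estimator equals one half under no effect only when there are no ties. Its null value depends on mortality, which is not known in advance, so neither the estimate nor its interval can be read without further information. It is also the only effect estimate with an interval that the article specifies for the primary outcome.

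**Working it through.** **Inputs (Sample size {14}).** Mortality: "Ninety-day mortality 45% in the control group, and 40% in the intervention group". VFD at day 60, mean ± SD: "28 ± 16.5 in the control group and 34.5 ± 13 in the intervention group". Sample size 100 per arm. Expected mortality range 34–50%.

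**Assumption.** The VFD figures are taken as roughly normal among survivors. They cannot be all-patient values with deaths set to 0. In the control arm the implied survivor variance would be (16.5² + 28²)/0.55 − (28/0.55)² ≈ −671, which is impossible.

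**The plan's own figure.** The stated criterion is: "The power was computed as the proportion of tests with a bilateral *p*-value < 0.05", with power above 80% at 100 per arm. Simulating the procedure as written (4000 datasets) gives 0.80 to 0.82. The inputs are therefore being read as the protocol used them.

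**Formulas.** Let pC and pT be mortality in the control and ULTV arms, and q the chance that a surviving ULTV patient has more VFD than a surviving control. Before VFD ties:

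- P(win) = (1 − pT)·pC + (1 − pT)(1 − pC)·q
- P(loss) = pT·(1 − pC) + (1 − pT)(1 − pC)(1 − q)
- P(tie) = pT·pC

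**No effect.** With pT = pC = p and q = 0.5, P(win) = (1 − p²)/2.

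| Mortality in both arms | Both-dead ties | P(win) under no effect |
|---|---|---|
| 34% | 0.1156 | 0.442 |
| 40% | 0.1600 | 0.420 |
| 45% | 0.2025 | 0.399 |
| 50% | 0.2500 | 0.375 |

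With whole-day VFD limited to 0–60, simulation gives 0.396 at 45% mortality.

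**Planned benefit.** q = Φ(6.5/√(16.5² + 13²)) = Φ(6.5/21.01) = 0.6215.

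- P(win) = 0.60 × 0.45 + 0.60 × 0.55 × 0.6215 = 0.270 + 0.205 = 0.475
- P(loss) = 0.40 × 0.55 + 0.33 × 0.3785 = 0.220 + 0.125 = 0.345
- P(tie) = 0.40 × 0.45 = 0.180

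With whole-day VFD, P(win) is 0.472. In simulation the raw proportion exceeds 0.5 in only about 27–29% of trials.

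**Other mortality levels.** Keeping the relative mortality reduction (pT = pC × 40/45) and the same VFD effect:

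| Control mortality | Expected raw proportion | No-effect value at that mortality |
|---|---|---|
| 34% | 0.524 | 0.442 |
| 40% | 0.498 | 0.420 |
| 45% | 0.475 | 0.399 |
| 50% | 0.450 | 0.375 |

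A proportion of 0.45 is thus the expected benefit at 50% mortality and close to the no-effect value at 34%.

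**Interval read against 0.5.** The article does not name an interval method, so a U-statistic variance is assumed. With no effect and 45% mortality, the upper 95% limit lies below 0.5 in roughly 66–71% of simulated trials (100 per arm). At 34% mortality this falls to about 30–33%. Under the planned benefit the upper limit is below 0.5 in about 9% of trials and the lower limit above 0.5 in about 0.4%, so the interval usually straddles 0.5.

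**Counting half of the ties.** P(win) + 0.5·P(tie) is 0.399 + 0.101 = 0.500 under no effect at 45% mortality, and 0.5 at any other mortality. Under the plan it is 0.475 + 0.090 = 0.565. Equivalent measures under the plan are net benefit 0.475 − 0.345 = +0.130 (null 0) and win odds 0.565/0.435 = 1.30 (null 1). In simulation the half-tie estimate falls below 0.5 in about 6% of trials under the planned benefit. Under no effect its upper limit falls below 0.5 in about 3%.

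**The case against.** **The direction of effect is already in the planned output.** This stands. The mean ULTV score divided by the number of controls is exactly P(win) − P(loss). With 100 controls it averages about 0 under no effect and about +13 under the planned benefit. Together with the win proportion, loss and tie shares follow by subtraction. A reader might infer that the plan would conceal a real benefit, and the documents do not support that. What is missing is an interval on a scale with a known null.

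**The protocol never names 0.5.** This also stands. The proportion of wins is a coherent quantity, correctly described, and no decision is tied to its interval. The article does not contradict itself here; it fixes an estimator that is hard to read. The misreading as harm depends on a reader supplying 0.5.

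**Tie handling may be settled elsewhere.** The sentence cites a methods reference, and the full protocol is in additional files; neither was available for this check. But the article states a plain proportion of favorable pairs. If half-ties are intended, that sentence needs the same correction.

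**The estimate might be thought to disagree with the p-value.** A reader might infer this, but it cannot be attributed to the estimator. In the same simulations, the Mann-Whitney test applied to scores built against the opposite arm rejects in about 88% of datasets with no effect at 45% mortality. Such a p-value could disagree with a tie-adjusted measure just as well. That is a separate problem, which correcting the effect size does not resolve.

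**Conclusion.** The point holds as a badly fixed estimator. As written, the no-effect value is (1 − ties)/2: about 0.40 at 45% mortality and 0.442 to 0.375 over 34–50%, before VFD ties. This follows from the scoring rule alone and needs no assumption about the shape of the VFD distribution.

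The expected value under the planned benefit, about 0.47, does rest on reading the VFD figures as roughly normal in survivors. It should not be generalised into a claim that any true benefit gives a value below 0.5: at 34% control mortality the same relative effect gives about 0.52. The share of trials whose interval lies wholly below 0.5 under no effect depends on mortality and on an interval method that the article does not state.

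The consequence is one of interpretation. The primary effect estimate and its interval have no fixed reference and, if set against 0.5, lean toward harm.

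**What to change.** In Analysis of the primary outcome, replace the estimator sentence with one that defines the effect size as P(win) + 0.5 × P(tie), states that its no-effect value is 0.5, and names a U-statistic 95% confidence interval. Net benefit (null 0) or win odds (null 1) would serve equally well. Report the raw win, loss and tie proportions as description.

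The cost is one sentence and about one line of code, best settled before the comparative results are seen. Data collection and sample size are unaffected. The validity of the Mann-Whitney test on cross-arm scores needs its own review.
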